# Empagliflozin in improving exercise tolerance in HFpEF: study protocol for an open-label, randomized controlled study

**DOI:** 10.1186/s13063-026-09654-y

**Published:** 2026-04-07

**Keywords:** SGLT2i, HFpEF, HFmrEF, CPET, Exercise tolerance, Study protocol

## Abstract

**Introduction:**

Heart failure with preserved ejection fraction (HFpEF) constitutes nearly half of patients with heart failure, but there is still a lack of treatment options to improve prognosis. Empagliflozin is a new hypoglycemic medication classified as sodium glucose cotransporter 2 inhibitors (SGLT2i); nonetheless, its effects on exercise tolerance in HFpEF remain ambiguous. Additional clinical studies are necessary to clarify the effect of SGLT2i in HFpEF. This study aims to evaluate the efficacy and safety of empagliflozin on exercise tolerance in patients with heart failure with preserved ejection fraction without diabetes, using cardiopulmonary exercise testing.

**Methods and analysis:**

This study is a single-center, open-label, randomized controlled trial. We will randomly (1:1) assign 86 patients with an ejection fraction of more than 40% and class II–III heart failure to receive empagliflozin (10 mg once daily) or to maintain their original treatment regimen. The treatment duration will be 12 weeks. The primary endpoint is the evaluation of changes in peak oxygen uptake (peak VO2) after a 12-week period using cardiopulmonary exercise testing (CPET). The secondary endpoints encompassed additional parameters of CPET and echocardiography, N-terminal pro-B-type natriuretic peptide level, alanine aminotransferase level, aspartate transaminase level, estimated glomerular filtration rate level, New York Heart Association functional classification, and scores from the Minnesota Living with Heart Failure Questionnaire. Safety events associated with empagliflozin and CPET will be monitored.

**Discussion:**

We used peak oxygen uptake, the gold standard for assessing exercise tolerance, to evaluate the efficacy and safety of empagliflozin in treating non-diabetic patients with HFpEF. The improvement in quality of life of heart failure patients by SGLT2i will be objectively assessed.

**Trial registration:**

www.chictr.org.cn (ChiCTR2300072908). Registered on 04 July 2023.

**Supplementary Information:**

The online version contains supplementary material available at 10.1186/s13063-026-09654-y.

## Background

Heart failure (HF) is a group of complex clinical syndromes characterized by abnormal structural and/or function of the heart due to a variety of causes, leading to impaired ventricular contraction and/or diastolic function. In patients with heart failure, those with heart failure with preserved ejection fraction (HFpEF) make up a large proportion. Community data on the prevalence and incidence of HFpEF indicate that approximately 50% of patients with the clinical syndrome of heart failure have a preserved ejection fraction [1]. HFpEF is a highly prevalent, complex, and heterogeneous disease. The universally accepted pathophysiology of HFpEF includes left ventricular diastolic dysfunction, pulmonary vascular dysfunction and right ventricular dysfunction [2]. Currently, HFpEF lacks effective therapies, and clinical treatment primarily focuses on symptom alleviation.

Sodium-glucose cotransporter 2 inhibitors (SGLT2i) is a rising star among antidiabetic drugs. Increasing research has confirmed that SGLT2i have effects beyond glucose lowering, providing benefits to multiple organs such as the heart and kidneys, particularly in cardiovascular events, with a predominant focus on heart failure. SGLT2i exert therapeutic effects in heart failure through multiple mechanisms, including the inhibition of cardiac inflammation and fibrosis, antagonism of sodium retention, and enhancement of glomerular function [3]. SGLT2i can improve myocardial energy metabolism, promote ketone production and utilization, and decelerate the progression of heart failure [4]. Consequently, SGLT2i are gradually becoming first-line medications for the treatment of heart failure.

Nonetheless, owing to the substantial disparities in the pathophysiology of HFpEF, clinical studies have failed to confirm that ACEI/ARB and beta-blockers can improve the prognosis or reduce the mortality rate of HFpEF patients. Consequently, there is a lack of evidence-based medical evidence for the treatment of HFpEF. But increasing clinical studies have found that SGLT2i can confer cardiovascular benefits to patients with HFpEF. The renowned randomized trials, EMPEROR-Preserved trial and DELIVER trial, have demonstrated that SGLT2i empagliflozin and dapagliflozin can reduce the composite risk of cardiovascular death or heart failure hospitalization in patients with HFrEF and HFpEF [5, 6]. A meta-analysis revealed that the concurrent use of ARNI, MRA, and SGLT2i exerts potent anti-heart failure effects [7]. SGLT2i in the growing role of HfpEF. Further clinical studies are still needed to confirm the role of SGLT2i in HFpEF.

Exercise intolerance is a symptom of HF, which is in connection with an increasing risk of death. Cardiopulmonary exercise testing (CPET) a diagnostic examination that assesses cardiopulmonary function. It involves a series of assessments conducted by measuring changes in cardiopulmonary function and related parameters during exercise. In individuals with heart disease, CPET can quantify the extent to which exercise limitations are attributable to cardiac factors. Peak oxygen uptake (peak VO2) is considered the foremost standard for evaluating exercise intolerance in individuals with HF [8]. Peak VO2 is also an important predictor of mortality in patients with HFpEF [9]. The parameters of peak VO2, percent predicted peak VO2,and exercise duration in CPET had the strongest ability to predict mortality [9].

We designed the study to evaluate the efficacy of empagliflozin on exercise tolerance in patients with HFpEF.

## Methods and design

### Design

This study is designed as a single-center, open-label, randomized controlled trial. After the screening period, eligible patients are randomly assigned (1:1 randomization) to receive either empagliflozin, 10 mg per day, or to continue with the original treatment plan. Figure 1 illustrates the design and procedures through the trial.

**Fig. 1 Fig1:**
[figure not shown]
Study design ECG, electrocardiogram; UCG, ultrasound cardiogram; CPET, cardiopulmonary exercise testing; Laboratory tests: complete blood count, serum lipids and biochemical tests. MLHFQ, Minnesota Heart Failure Quality of Life Scale

### Study hypothesis

Empagliflozin can improve exercise tolerance of patients with HFpEF.

### Study population, eligibility criteria, and recruitment

Participants are men or women aged 18 to 75 years, who have New York Heart Association (NYHA)functional class II–III chronic heart failure and a left ventricular ejection fraction of more than 40% (encompassing both HFmrEF and HFpEF, as in the EMPEROR-Preserved trial). The protocol requires patients to have an N-terminal pro–B-type natriuretic peptide (NT-proBNP) level of more than 300 pg per milliliter and estimated glomerular filtration rate (eGFR) more than 30 ml/min/1.73 m^2^.

The study primarily excludes patients with diabetes, severe liver or kidney dysfunction, as well as those with other conditions deemed unsuitable for inclusion. The key inclusion and exclusion criteria are listed in Table 1.

**Table 1 Tab1:** Inclusion and exclusion criteria

**Inclusion criteria**
(1) Aged 18 to 75 years, male or female;
(2) Patients with chronic HF (NYHA class II and III) diagnosed for at least 3 months and currently in HF NYHA class II-III;
(3) LVEF>40%；
(4) NT-proBNP >300 pg/mL;
(5) eGFR≥30ml/min/1.73m^2;
(6) Able to understand and voluntarily sign the informed consent form;
**Exclusion criteria**
(1) Diabetes;
(2) Acute coronary syndrome whihin the last 2 months or planned coronary revascularization during the trial;
(3) Atrial fibrillation, cardiovascular and cerebrovascular events related to atrial fibrillation in the last 3 months;
(4) Hepatic dysfunction, defined by serum levels of transaminases more than three times the upper limit of normal at screening;
(5) Using SGLT2i within 4 weeks prior to randomization;
(6) Diseases that affect the results of CPET include arthropathy, peripheral vascular disease, lung disease and other diseases;
(7) The subject's resting ECG has the following abnormalities: (a) ventricular pre-excitation syndrome; (b) ventricular pacing rhythm; (c) resting ST segment depression of more than 2 mm; (d) left bundle branch block or any intraventricular conduction delay with QRS duration greater than 120 ms；
(8) Congenital heart defects, progressive decompensated congestive heart failure, severe valvular disease, hypertrophic obstructive cardiomyopathy, severe uncontrolled hypertension (sitting systolic blood pressure >180mmHg or diastolic blood pressure >110mmHg), severe anemia, suspected or known arterial dissection, acute myocarditis or pericardial effusion, active endocarditis, thrombophlebitis, or pulmonary embolism.
(9) History of bleeding tendency, cerebral hemorrhage, or epilepsy requiring anticonvulsant medication.
(10) Pregnant woman or breastfeeding woman.
(11) Participated in any other trials or use of any investigational drugs within the 30 days prior to enrollment.
(12) Drug abuse. The patient has a history of alcohol abuse or known drug dependence in the past 2 years.
**Withdrawal Criteria**
(1) Any suspected drug-related serious adverse events (e.g., allergic reactions).
(2) Recurrence of acute heart failure or sudden severe dysfunction of organs such as the liver or kidneys.
(3) Pregnancy.
(4) Major protocol deviations. After randomization, it is found that the subject does not meet the inclusion criteria of the study protocol or does not follow the requirements of the study protocol, and continuing to participate in the study may pose unacceptable risks to the subject's health.
(5) Loss to follow-up. The subject does not return to the clinic and cannot be successfully contacted. Information on attempts to contact the subject must be documented.
(6) Voluntary withdrawal. The subject (or the subject's legal representative) wishes to withdraw from the study. The reason for withdrawal should be recorded in the case report form.
(7) Study termination. The study is terminated by the sponsor, ethics committee, or regulatory authority.

*CPET *cardiopulmonary exercise testing, *ECG* electrocardiogram

The study will be conducted at The Third Affiliated Hospital of Guangzhou Medical University. Patients will be recruited by researchers describing this study in the outpatient service and inpatient departments. Posters containing study information will also be used within the hospital. Every patient will sign informed consent prior to enrollment.

### Randomization and allocation

Randomization sequences will be generated by an independent statistician using SAS 9.4, with a 1:1 allocation ratio and variable block sizes. To ensure allocation concealment, the sequence will be implemented using sequentially numbered, opaque, sealed envelopes. After a participant is enrolled, the investigator will open the next sequentially numbered envelope in the series to reveal the assignment. This trial is open-label; no blinding will be used after assignment.

### Blinding

This trial is not blinded. We currently lack the conditions to produce placebos.

### Intervention

Patients in the empagliflozin group will receive empagliflozin (Boehringer Ingelheim Pharma GmbH & Co. KG) 10 mg once daily in addition to the standard medication regimen. The control group will continue with the original treatment regimen. All patients will be treated for 12 weeks.

### Concomitant medication

All patients will receive treatment for HFpEF according to the authoritative guidelines on heart failure therapy released by the ESC in 2021 [10]. At the same time, patients will feel the need to take other medications, which will be recorded and analyzed.

### Outcomes

#### Primary outcome

The primary outcome is the variation in peak VO_2_ during the study period.

#### Secondary outcomes

Secondary outcomes include the following: (a) Changes in peak VO2/HR, anaerobic threshold (AT), and VE/VCO2 evaluated by cardiopulmonary exercise testing (CPET); (b) variations in left ventricular ejection fraction (LVEF), left ventricular end-diastolic volume (LVEDV), left atrial volume (LAV), E/E’, and pulmonary artery pressure (PAP) as evaluated by echocardiography; (c) changes from baseline in levels of alanine aminotransferase (ALT), aspartate aminotransferase (AST), estimated glomerular filtration rate (eGFR), and N-terminal pro-B-type natriuretic peptide (NT-proBNP) at week 12; (d) changes from baseline in New York Heart Association (NYHA) functional class and Minnesota Heart Failure Quality of Life Questionnaire (MLHFQ) scores at week 12 (see Table 2).

**Table 2 Tab2:** Primary and secondary endpoints

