**Secondary endpoint**
The changes of the following parameters from baseline to week 12
1. Other CPET parameters
- peak VO_2_/HR
- AT
- VE/VCO_2_
2. Ultrasound cardiogram
- LVEF
- LVEDV
-LAV
- E/E ’
- PAP
3. New York Heart Association functional class
4. Minnesota Heart Failure Quality of Life Scale.
5. NT-proBNP.
6.ALT/AST/eGFR

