### Statistical analysis

Statistical analysis will be conducted using SAS 9.4. All statistical tests will be two-tailed, and a *p*-value of less than 0.05 will be considered statistically significant, unless otherwise specified.

For continuous data, statistical descriptions will include counts, means, standard deviations, medians, minimum and maximum values, and upper and lower quartiles. For categorical data, counts and percentages will be used for statistical descriptions. Between-group comparisons of continuous data will be conducted using *t*-tests or rank-sum tests, while categorical data will be compared using chi-square tests or Fisher’s exact test. Non-parametric methods, such as the Wilcoxon rank-sum test, will be employed for ordinal data. Continuous data will be presented as mean ± standard deviation (x ± s). Normality tests will be conducted first, and if both groups meet the assumptions of normality and have equal variances, a *t*-test will be used for between-group comparisons. Otherwise, we will consider the non-parametric Wilcoxon rank-sum test.

Missing data for the primary efficacy endpoint will be addressed using multiple imputation under the assumption of missing at random. Twenty imputed datasets will be generated using predictive mean matching incorporating baseline characteristics. The pooled estimates from the imputed datasets will be used for the primary analysis. Additionally, a complete-case analysis will be conducted as a validation to evaluate the robustness of the results.

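### NT-proBNP is analysed as a change in level with a rank-test fallback; ANCOVA on the log scale would be moderately more efficient and would give the between-arm estimate that the rank test lacks (minor)

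*Protocol article*

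**What the plan says.** Secondary outcome (c) in the protocol article, assessed after 12 weeks, is "changes from baseline in levels of alanine aminotransferase (ALT), aspartate aminotransferase (AST), estimated glomerular filtration rate (eGFR), and N-terminal pro-B-type natriuretic peptide (NT-proBNP". Table 2 repeats the definition for all secondary endpoints: "The changes of the following parameters from baseline to week 12". Neither place mentions a logarithm, a ratio or a percentage change, so an arithmetic difference in pg/mL is the natural reading.

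Table 1, inclusion criterion (4), requires "NT-proBNP >300 pg/mL" and sets no ceiling.

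Under Statistical analysis, "Continuous data will be presented as mean ± standard deviation (x ± s"), and "Between-group comparisons of continuous data will be conducted using *t*-tests or rank-sum tests". The choice is conditional: "if both groups meet the assumptions of normality and have equal variances, a *t*-test will be used for between-group comparisons". Failing that, the plan says a Wilcoxon rank-sum test would be considered. The same section also plans medians and quartiles among the descriptive statistics. ANCOVA is named only for the primary endpoint, peak VO2.

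**The concern.** NT-proBNP has a floor at entry and no ceiling, so its values are likely to be right-skewed, and the size of a change in pg/mL depends on where the patient started. A 20% fall is 80 pg/mL from 400 and 800 pg/mL from 4,000. A 50% fall from 400 is only 200 pg/mL, so it counts for less than the 20% fall from 4,000, whether the changes are averaged or ranked.

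Two things are at stake. A real proportional reduction is somewhat more likely to be missed. And when the rank test is used, the plan names no between-arm estimate: the reader gets a p-value from ranks beside means and SDs in pg/mL, and the two need not agree. NT-proBNP is the only blood marker of heart failure among the endpoints of this open-label trial, so a usable effect size is worth having.

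**Working it through.** **1. The plan's own figure.** The sample size is for peak VO2: n = 2 × [2.4 × (1.96 + 0.8416) / 1.6]² = 35.3, so 36 per group, as stated. With 43 randomised per group and 20% dropout, 43 × 0.8 = 34.4, so 34 evaluable per arm is used below. The document gives no power, SD or effect for NT-proBNP. **All distribution inputs below are therefore assumptions.**

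**2. Which test would be used.** The stated rule was simulated as Shapiro-Wilk in each arm plus Levene, then t-test or Wilcoxon, on pg/mL changes. At 34 per arm about 85-98% of trials went to Wilcoxon. In a second set of assumptions, at 36 and 43 per arm, 90-100% did.

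**3. Type I error.** About 4-6% for every method.

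**4. Influence of high patients on the mean.** In the second set, the most extreme 10% of patients carried about 64-81% of the variance of the pg/mL change. This bears on the mean difference and its SD, and much less on the rank p-value.

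**5. Power, first set.** Log-normal, median 700 pg/mL before truncation at 300, log-SD s = 0.7 or 0.9, correlation 0.8, 34 per arm, two-sided 0.05:

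| s | True ratio | Stated rule | ANCOVA on logs | Loss (points) |
|---|---|---|---|---|
| 0.7 | 0.80 | 43% | 56% | 13 |
| 0.7 | 0.70 | 79% | 93% | 14 |
| 0.9 | 0.80 | 26% | 38% | 12 |
| 0.9 | 0.70 | 56% | 76% | 20 |

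A separate run of this setting gave 29-42% against 39-57% at ratio 0.80 and 55-79% against 75-93% at ratio 0.70. Together the loss is roughly 10-20 points.

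**6. Check of the log ANCOVA column by formula.** Residual log-SD = s√(1 − 0.8²) = 0.6s, so 0.42 or 0.54. SE = residual SD × √(2/34), so 0.102 or 0.131. With |ln 0.80| = 0.223 and |ln 0.70| = 0.357:
- s = 0.7: z = 2.19 and 3.50, so Φ(z − 1.96) is about 59% and 94%.
- s = 0.9: z = 1.70 and 2.72, so about 40% and 78%.

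These normal approximations lie slightly above the simulated values, as expected.

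**7. Power, second set.** Underlying median 600-800 pg/mL cut at 300, log-SD 0.6-1.0, within-patient log-change SD 0.4-0.6, ratio 0.75, comparator an unadjusted t-test on the log ratio:
- 36 per arm: stated rule 41-79%, log ratio 51-86%.
- 43 per arm: 50-85% and 58-91%.

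Taken setting by setting, the loss is about 7-12 points. A further run with the same nominal inputs as step 5 gave 29-46% (rank-sum) against 36-53% (log ANCOVA) at ratio 0.80, and 61-82% against 72-90% at 0.70, which is 7-11 points. The size therefore depends on how the baseline and week-12 values are modelled.

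**8. ALT and AST.** Assumed median 22, ceiling 120 (three times an assumed upper limit of 40), log-SD 0.35-0.5, change SD 0.25-0.35, ratio 0.85, 36 per arm: stated rule 43-72%, log ratio 49-77%, a loss of about 3-7 points.

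**The case against.** The strongest reply is that the plan already deals with skew. The t-test is allowed only after normality and equal variance are met, and step 2 shows that NT-proBNP would rarely pass. A reader might infer that a few patients with very high values would decide the test result. The documents do not support that, because the rank test limits their influence. A reader might also infer a large loss of power by comparing the log analysis with a plain t-test on pg/mL, where the gap in step 7's settings is about 13-32 points. That is not the test the plan would usually reach. Both parts of the reply stand.

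It also stands that medians and quartiles are already planned, that type I error is sound, and that a purely proportional effect on log-normal data is the setting in which a log analysis does best.

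Extending the point to ALT and AST is tempting but fails. Exclusion criterion (4) sets a ceiling: "Hepatic dysfunction, defined by serum levels of transaminases more than three times the upper limit of normal at screening". The gain there is small.

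Finally, a fuller analysis plan that is not shown could set the scale. That would answer mere silence, but this article states a change in level, a mean ± SD presentation and a test. It is those stated choices that can be improved.

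The rank fallback does not remove the scale problem, since raw pg/mL changes are still what is ranked. It brings no named between-arm estimate, and the plan says only that it would be considered.

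**Conclusion.** The point holds for NT-proBNP alone, as a matter of efficiency and interpretability and not of validity. Under the stated rule the loss against ANCOVA on logs is roughly 10-20 power points with the inputs of step 5; under the other assumptions in step 7, and against an unadjusted log ratio, it is about 7-12 points. None of these inputs comes from the documents. Independently of the power figures, the rank test would leave the endpoint without a between-arm effect size, and the mean difference in pg/mL that might stand in for one would be dominated by high values. Severity is minor: this is a secondary endpoint with no stated power.

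**What to change.** In secondary outcome (c) and in the statistical analysis section, state that log(week-12 NT-proBNP) will be analysed by ANCOVA with log(baseline) and arm. Report the between-arm ratio of geometric means at week 12 with its 95% CI, and summarise each arm by geometric mean or median (IQR). ALT, AST and eGFR can stay as they are.

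The cost is about a sentence in each place and no new data. The one downside is that the effect is reported as a ratio and not in pg/mL.

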**Primary endpoint**
The variation in peak VO_2_ during the study period.
**Secondary endpoint**
The changes of the following parameters from baseline to week 12
1. Other CPET parameters
- peak VO_2_/HR
- AT
- VE/VCO_2_
2. Ultrasound cardiogram
- LVEF
- LVEDV
-LAV
- E/E ’
- PAP
3. New York Heart Association functional class
4. Minnesota Heart Failure Quality of Life Scale.
5. NT-proBNP.
6.ALT/AST/eGFR
**Safety endpoints**
Hypoglycemia,hypotension, deterioration of kidney function, urinary tract infection, elevated LDL cholesterol.

*CPET *cardiopulmonary exercise testing

### Study timelines

#### Screening visit (Day −14 ± 3)

The timeline and inspection items are listed in Table 3. At the screening visit, participants will receive ECG, eligibility laboratory tests, vital signs measurement, and drug history registration. Laboratory data will include urine pregnancy testing, complete blood count, biochemical indexes, NT-proBNP.

**Table 3 Tab3:** Schedule of assessments

Timelines	Screening Visit	Baseline Visit	Follow-Up Visit
Week	−2	0	12
Day	−14±3	0	84±3
Informed consent	✓	X	X
Inclusion/exclusion criteria	✓	✓	X
Concomitant medication	✓	✓	✓
Vital signs	✓	✓	✓
Physical examination	✓	✓	✓
urine pregnancy testing^a^	✓	X	X
12-lead ECG	✓	X	✓
CPET	X	✓	✓
Cardiac ultrasound	X	✓	✓
Laboratory tests^b^	X	✓	✓
New York Heart Association functional class	X	✓	✓
Minnesota Heart Failure Quality of Life Scale	X	✓	✓
Medical history	✓	✓	X
Adverse events^c^	✓	✓	✓

^a^Urine pregnancy testing for women of reproductive age

^b^Laboratory tests include: complete blood count, eGFR, ALT, AST, NT-proBNP

^c^Adverse events include: urinary system, hypoglycemia, renal function damage, etc

✓ indicates that the item must be completed at that time

X indicates that the item is not required at that time

